## Abstract

**Background:**

Multiple sclerosis (MS) is an inflammatory and neurodegenerative disease, characterised by oligodendrocyte death and demyelination. Oligodendrocyte progenitor cells can differentiate into new replacement oligodendrocytes; however, remyelination is insufficient to protect neurons from degeneration in people with MS. We previously reported that 4 weeks of daily low-intensity repetitive transcranial magnetic stimulation (rTMS) in an intermittent theta-burst stimulation (iTBS) pattern increased the number of new myelinating oligodendrocytes in healthy adult mice. This study translates this rTMS protocol and aims to determine its safety and tolerability for people living with MS. We will also perform magnetic resonance imaging (MRI) and symptom assessments as preliminary indicators of myelin addition following rTMS.

**Methods:**

Participants (*N* = 30, aged 18–65 years) will have a diagnosis of relapsing-remitting or secondary progressive MS. ≤2 weeks before the intervention, eligible, consenting participants will complete a physical exam, baseline brain MRI scan and participant-reported MS symptom assessments [questionnaires: Fatigue Severity Scale, Quality of Life (AQoL-8D), Hospital Anxiety and Depression Scale; and smartphone-based measures of cognition (electronic symbol digit modalities test), manual dexterity (pinching test, draw a shape test) and gait (U-Turn test)]. Participants will be pseudo-randomly allocated to rTMS (*n*=20) or sham (placebo; *n*=10), stratified by sex. rTMS or sham will be delivered 5 days per week for 4 consecutive weeks (20 sessions, 6 min per day). rTMS will be applied using a 90-mm circular coil at low-intensity (25% maximum stimulator output) in an iTBS pattern. For sham, the coil will be oriented 90° to the scalp, preventing the magnetic field from stimulating the brain. Adverse events will be recorded daily. We will evaluate participant blinding after the first, 10th and final session. After the final session, participants will repeat symptom assessments and brain MRI, for comparison with baseline. Participant-reported assessments will be repeated at 4-month post-allocation follow-up.

**Discussion:**

This study will determine whether this rTMS protocol is safe and tolerable for people with MS. MRI and participant-reported symptom assessments will serve as preliminary indications of rTMS efficacy for myelin addition to inform further studies.

**Trial registration:**

Australian New Zealand Clinical Trials Registry ACTRN12619001196134. Registered on 27 August 2019

## Administrative information

Note: the numbers in curly brackets in this protocol refer to SPIRIT checklist item numbers. The order of the items has been modified to group similar items (see http://www.equator-network.org/reporting-guidelines/spirit-2013-statement-defining-standard-protocol-items-for-clinical-trials/).

Role of sponsor {5c}	Funders and study sponsor were not directly involved in study design and will not be involved in collection, management, analysis, or interpretation of data, or the decision to submit for publication. The study sponsor is responsible for the overall conduct of the study, research governance, insurance and indemnity. The sponsor may determine to discontinue the study if it is in the best interest of participants. The sponsor is also responsible for archiving study records and participant data for a minimum of 15 years.

## Introduction

### Background and rationale {6a}

Multiple sclerosis (MS) is a chronic neurological condition; is the leading cause of non-traumatic disability in young adults, affecting over 2.3 million people worldwide; and in 2017, was estimated to cost the Australian community AUD$1.75 billion [1]. MS was long considered an autoimmune disease; however, it has an underlying neurodegenerative pathology that can persist even in the absence of immune cell attack [2]. Oligodendrocytes are the central nervous system cells that produce myelin and provide metabolic support to neurons [3]. Their death during MS pathogenesis leads to the formation of demyelinated brain lesions, neurodegeneration and disability accrual [4]. MS clinical management involves modulating or suppressing the immune system, which can be effective in reducing relapse frequency in relapsing remitting MS, but can also have significant side effects [5]. While some remyelination occurs in people with MS, the degree of remyelination is insufficient and ultimately fails [6]. Preclinical studies indicate that remyelination can rapidly improve altered neuronal function caused by myelin loss, and thus could potentially protect neurons from degeneration and mitigate the accrual of disability in people with MS [7]. The current drugs available for MS management may slow but do not stop disease progression, and no treatments actively promote remyelination.

A series of in vitro and in vivo laboratory studies have shown that increasing neuronal activity can increase oligodendrogenesis and facilitate myelin production [8–10]. Repetitive transcranial magnetic stimulation (rTMS) is a non-invasive way to modulate neuronal activity [11]. rTMS has been used in clinical and research settings for several decades and utilises electromagnetic induction to painlessly stimulate the brain and alter cortical excitability [12]. In our preclinical studies, we delivered low-intensity rTMS daily for up to 1 month to the brain of adult mice. Mice that received rTMS in an intermittent theta-burst stimulation (iTBS) pattern doubled the number of new oligodendrocytes in the stimulated cortex. Increased numbers of oligodendrocytes were already present after 2 weeks of stimulation but they were immature and did not produce myelin. When the stimulation was stopped at this point, the new cells failed to survive and myelinate. However, when stimulation was sustained for 4 weeks, the new oligodendrocytes matured, elaborated myelin internodes and survived after the stimulation ceased [13]. In this study, we translate this low-intensity rTMS protocol and evaluate its safety for people with MS.

### Risks

rTMS is generally well-tolerated and considered safe with common side effects being mild, such as scalp discomfort or tingling during stimulation and headaches or dizziness, which generally subside soon after stimulation. Although extremely rare, other side-effects associated with rTMS include hearing loss due to the noise from the coil and its proximity to the ear, or seizure induction, particularly in those who have epilepsy or other seizure histories [14, 15]. rTMS is most commonly applied at intensities ranging from 80 to 120% of resting motor threshold (~30–65% maximum stimulator output, MSO) using a figure of 8 coil to direct the highest intensity to a focal target region [16]. The lower intensity (25% MSO) and diffuse stimulation by use of a circular coil, markedly reduces risks of side-effects, which increase with intensity of stimulation [15]. rTMS has not been associated with detrimental effects on fatigue, anxiety or depression in people with MS or in healthy populations; therefore, the risk of exacerbating or causing these symptoms appears low.

rTMS has been widely used in clinical trials and research settings, with effects of stimulation depending on stimulation frequency, intensity, region and focality of stimulation and number of sessions [12]. Previous studies applying various forms of rTMS suggest that it is safe in people with MS, and a recent review concluded probable efficacy (level B evidence) of focal iTBS to improve lower limb spasticity (reviewed by Lefaucheur et al. 2020 [16]). Small studies using various rTMS protocols suggest potential benefits of rTMS to treat other MS symptoms including fatigue and depression [17], working memory performance [18] and manual dexterity [19]. This will be the first study to deliver and evaluate the safety of this low-intensity rTMS protocol and collect exploratory data on the utility of rTMS to promote myelin addition to the brain in people with MS.

The principal aim of this study is to determine whether low-intensity rTMS is safe and tolerated by people with MS, when delivered in 20 sessions over a maximum of 5 consecutive weeks. We will use magnetic resonance imaging (MRI) and MS symptom assessments to indicate whether rTMS is able to increase myelin addition or improve other aspects of MS symptomology, which we will use to inform future, larger scale efficacy studies.

## Objectives {7}

### Primary objective

To determine if low-intensity rTMS using an iTBS pattern, delivered across 20 sessions over a maximum of 5 weeks, is safe and tolerable for people living with MS.

### Secondary objectives

To determine if a 5 days per week treatment regime is feasible for people with MS.To determine if the sham protocol is sufficient to maintain participant blinding.To determine if there is any evidence that rTMS alters myelin addition as detected using MRI measurements, to warrant further analysis in a phase II efficacy trial.To explore if there is any benefit of rTMS to MS symptoms (anxiety and depression, quality of life, fatigue, cognition and motor symptoms).

## Trial design {8}

Randomised placebo (sham) controlled, parallel design with 2:1 ratio of participants in the active rTMS group compared to the sham control (placebo) group. Phase 1 safety, feasibility and exploratory framework.

## Methods: participants, interventions and outcomes

### Study setting {9}

This study will be conducted at a single site: Clinical Research Facility at the Medical Sciences Precinct (MSP), University of Tasmania (UTAS), Tasmania, Australia.

### Eligibility criteria {10}

A person will be eligible to participate if they are age 18–65 years with an MS diagnosis provided by an MS neurologist; have been stable (on or off MS treatment) and relapse free for 3 months, with an Expanded Disability Status Scale (EDSS) between 1.5 and 6; are willing and able to travel to the study site every weekday for 4 consecutive weeks; and are capable of providing informed consent.

A person will be ineligible to participate if they:(i).Have metal inside their head or body (i.e. cardiac pacemaker) as metal may be affected by the magnetic field generated by rTMS but will certainly respond to the magnetic field generated by MRI.(ii).Are pregnant or intend to become pregnant, as the known influence of pregnancy hormones on myelination, remyelination and MS relapse [20] could confound results.(iii).Have a history of seizures, epilepsy, serious head trauma*, significant and ongoing substance abuse*, stroke, brain surgery, bipolar disorder, mania, claustrophobia or uncontrolled migraines* (including receiving tricyclic antidepressants, neuroleptics or antiseizure medication for the treatment of any indications listed here). These exclusion criteria are standard for rTMS studies and are based on theoretical or potential, rather than proven risk. For example, epilepsy, brain trauma and stroke can impact the structure of the neuronal circuitry and can result in people having a lower seizure threshold and could therefore increase the potential risk of seizure induced by rTMS.(iv).Have an EDSS ≤1 or ≥6.5. This exclusion criteria ensures that all participants are mobile and require no more than a walking cane for support, so are still mobile enough to attend study visits. People with more severe disability have significant neuron loss and chronic lesions, making them less able to benefit from the hypothesised remyelination effects of rTMS. We include people with an EDSS between 1.5 and 6, who likely have less neuron loss and are the most likely responders.(v).Previously received transcranial magnetic stimulation. Such people will have experienced the sensation associated with rTMS previously. This exclusion criterion is to maintain blinding of the participant.(vi).English illiterate or limited spoken English proficiency (to enable informed consent, participant reported outcomes and concomitant medication reporting at each visit). Participants able to provide a suitable translator/interpreter for the duration of the study (including phone calls, questionnaires and visits) may be included. Translators do not need to be accredited and can be a suitable friend or family member of the participant.(vii).Currently involved in another interventional clinical trial.(viii).Do not have access to a smartphone (to enable cognitive function tests to be completed using the Floodlight Open smartphone app).

An eligibility questionnaire has been developed to screen potential participants based on the criteria above (adapted from [21]. If the answer is “yes” to any of the exclusion criteria, participants will be informed they are not eligible for this trial. Eligible participants will be invited to visit 1 and provided a participant information sheet.

*Note: At the discretion of the clinical PI, participants with previous minor head trauma (e.g. concussion) without surgical intervention may be included if there are no ongoing clinical signs directly attributable to traumatic brain injury. Participants with resolved substance abuse may be included if the substance abuse has been resolved for 5 or more years, and therefore, substance use during the trial would be unlikely. Participants with a history of migraine may be included, at clinical PI discretion, if migraines are well-managed, infrequent (<1 per month) and not complicated, or if migraines have not occurred for at least 1 year before eligibility screening and trial enrolment. This criterion is intended to exclude those who are potentially at a higher risk of migraine adverse reactions to rTMS.

### Who will take informed consent? {26a}

A suitably trained, qualified and delegated researcher will obtain informed consent. Researchers will ensure participants understand what is involved as well as the risks. They will explain that this is a safety and feasibility trial, and that this intervention programme has not been delivered to people with MS before. Participants will be required to be fully informed with all questions answered, and required to provide their written informed consent form prior to any procedure being performed.

### Additional consent provisions for collection and use of participant data and biological specimens {26b}

Consent will also include a statement on future use of data collected. Biological specimens will not be collected. The participants will consent to have their referring clinician/neurologist informed of their participation in the study as well as relevant health outcomes and any serious adverse events that may occur.

### Interventions

#### Explanation for the choice of comparators {6b}

We will compare rTMS to sham (control) treatment groups. Participants are not required to stop concomitant MS treatments while on the study; thus, they will not be deprived of treatment while in this study. Sham control is the most rigorous comparator for assessing the safety or tolerability of the rTMS intervention. An assessment of efficacy is not the primary outcome for this study, but we will assess the capacity of our sham protocol to maintain participant blinding to inform a future phase II study.

#### Intervention description {11a}

Participants will receive rTMS or sham stimulation 5 days per week (weekdays) ideally over 4 consecutive weeks (20 sessions total). A maximum gap of 3 days is allowed between sessions, with all 20 sessions being delivered within a maximum of 5 consecutive weeks. rTMS will be delivered using a Magstim Rapid2 (Magstim Rapid2 package part numbers: 3012-00 Rapid2 Mainframe – 50Hz; 3013-00 Single Power Supply Unit; 3022-00 User Interface; Magstim Ltd, Whitland, UK) and Magstim 90mm standard circle coil (part number: 3193-00, Magstim Ltd. Whitland, UK). Participants will be seated upright in a comfortable reclinable chair, positioned so that the participant cannot see the Magstim Rapid2 user interface screen. The stimulation intensity will be set at 25% maximum stimulator output and parameters set for iTBS pattern: bursts of 3 pulses at 50Hz, repeated at 5Hz for a 2-s period (10 bursts), followed by an 8 sec gap (10-s cycle time), repeated for 20 cycles (600 pulses, 3 min) [22].

Coil target position will be determined relative to the vertex (top centre point of scalp, where sagittal and coronal planes intersect), found using a flexible tape measure and marking the mid-point between the nasion and inion, and pre-auricular (ear landmark) on each side, respectively. From the vertex, the target coil position will be marked with a whiteboard marker at 2cm lateral and aligned with the vertex in the anterior-posterior axis on both the left and right sides of the scalp. For rTMS delivery, the circular rTMS coil will be oriented so that the plane of the coil is tangential to the scalp and the central hole over the target mark. The coil handle will be pointing backwards, at 45° to the scalp midline. By positioning the circular coil in this way, we can stimulate a broad cortical area including frontal and parietal regions, consistent with our preclinical protocol [13]. Stimulation of the left or right hemisphere first will be counter-balanced between participants, but for individual participants will be consistent between sessions. After completing the 3 minutes of iTBS to the first hemisphere, the coil is then flipped and positioned to stimulate the second hemisphere for a further 3 minutes. Flipping the coil between hemispheres ensures that both hemispheres of the brain receive anteroposterior-induced current on the lateral portion of the coil for the second phase component of the biphasic pulse (i.e. side ‘A’ against the scalp of the right hemisphere results in an anti-clockwise current in the coil; side ‘B’ against the scalp on the left hemisphere results in a clockwise current flow in the 2^nd^ phase). Neuronal excitability is sensitive to the direction of the induced current and with lower intensity (below motor threshold) stimulation, only the anteroposterior induced-current direction in the effective (second) component of the biphasic pulse results in enduring excitability changes [23].

For sham, the procedure will be the same except that the coil will be angled at 90° to the scalp surface (i.e. outer edge profile of the coil touching scalp target location), directing the magnetic field perpendicular to the brain, effectively preventing stimulation. This method of sham stimulation has been used previously and its inclusion is listed as a criterion for rTMS trial quality (reviewed in [24]), as it is effective for blinding to intervention allocation in TMS-naïve participants, and ensures clicking sounds and timing aspects of the procedure are consistent between groups.

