### Outcomes {12}

#### Primary outcomes

The primary outcome will be the incidence of treatment emergent adverse events (AE) and serious adverse events (SAE), recorded at each visit during the intervention phase. Incidence will be compared between rTMS and sham using the proportion of participants that had at least one AE against participants who experienced no AEs (each participant counted once). AEs leading to premature discontinuation from the study intervention and serious treatment-emergent AEs will be presented either in a table or a listing. A clinically acceptable difference between the rTMS and sham conditions in treatment emergent events is 10% for adverse reactions and 0% for suspected unexpected serious adverse reactions (SUSARs). We defined this clinically acceptable difference based on previously reported rates of the most common side effects in sham-controlled rTMS clinical trials for depression, which were headache (mean incidence rates of 16% sham vs. 28% rTMS; 12% difference) and scalp pain/discomfort (mean incidence rates of 15% sham vs. 39% rTMS; 24% difference) [25]. Clinical trials using rTMS for depression typically deliver higher intensity and longer duration stimulation, so we expect lower incidence rates of these common adverse reactions. Risk of serious adverse reactions is reduced by excluding participants who are potentially at higher risk of serious adverse reactions to rTMS (e.g. history of seizure) [14, 15].

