## Assignment of interventions: blinding

### Who will be blinded {17a}

Participants will be blind to intervention assignment. MRI raw images will be assessed by blinded researchers. Statistical analyses will be deidentified but unblinded due to the uneven group allocation ratio (2:1); however, researchers performing the statistical analyses will not be involved in participant recruitment, allocation or delivery of the intervention. Researchers delivering rTMS/sham will be unblinded to the intervention group as sham is achieved by changing the orientation of the rTMS coil to prevent the magnetic field from entering the brain. Adverse event data will be collected by the researcher delivering the intervention at each intervention visit and is therefore, also unblinded. Adverse event data will be assessed and graded by the clinical PI who will remain blind to allocations.

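### The sham's field direction is stated the wrong way round, and its field is reduced, not prevented, so rTMS-sham differences may be attenuated

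*Protocol article*

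**What the plan says.** All references are to the protocol article.

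- **Active position** (Intervention description {11a}): the coil is "oriented so that the plane of the coil is tangential to the scalp and the central hole over the target mark". The device is a "Magstim 90mm standard circle coil" run at 25% of maximum stimulator output.
- **Sham position** (same section): the procedure is otherwise unchanged, but "the coil will be angled at 90° to the scalp surface (i.e. outer edge profile of the coil touching scalp target location"). The stated result is "directing the magnetic field perpendicular to the brain, effectively preventing stimulation".
- **Abstract, Methods:** the sham orientation is described as "preventing the magnetic field from stimulating the brain".
- **Who will be blinded {17a}:** this has the strongest wording. Sham is achieved by "changing the orientation of the rTMS coil to prevent the magnetic field from entering the brain".
- **Primary outcomes:** safety is judged by a between-arm difference. "A clinically acceptable difference between the rTMS and sham conditions in treatment emergent events is 10% for adverse reactions", and 0% for SUSARs.
- **Explanation for the choice of comparators {6b}:** sham is presented as the most rigorous comparator for safety and tolerability.

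The article gives no measured or modelled field for the sham position.

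**The concern.** Two statements about the comparator do not fit the geometry that the article describes.

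First, a circular coil's field runs along its axis. Laid flat, the coil sends its field into the head at right angles to the scalp. Stood on edge, it sends its field along the scalp. The sham sentence therefore describes the active position.

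Second, turning the coil does not keep the field out of the head. With the outer edge on the target, part of the winding lies next to the scalp, carrying the same current as in the active arm.

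This matters because the safety, MRI and symptom comparisons are all rTMS against sham. If the sham delivers part of an active stimulus, the differences shrink. For a safety limit that is the anti-conservative direction, since a smaller difference looks more acceptable. For MRI and symptom outcomes the pull is towards no effect. The usual reassurance, that a weak field does nothing, is not readily available here, because the trial's premise is that low-intensity stimulation is biologically active.

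**Working it through.** The article gives no field figure, so there is nothing of its own to reproduce. The check has three steps.

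**1. Direction of the magnetic field**

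Inputs from the article: coil flat on the scalp (active), coil on edge at the target (sham), circular coil.

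Assumed: one loop of 45 mm radius, a 5 mm gap to the scalp, and a point 20 mm below the scalp.

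The Biot-Savart law, with the third axis pointing out of the scalp, gives these unit vectors:

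- Active, under the coil centre: (0, 0, 1), perpendicular to the scalp.
- Sham, under the contact point: (-1, 0, 0), parallel to the scalp.

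The sham field there has 0.36 of the active magnitude. So the stated direction is reversed, and the field does enter the head.

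**2. Induced electric field in cortex**

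Input from the article: the same output in both arms, so only geometry matters and the current cancels in the ratio.

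Assumed, because the article does not give them: spherical head of radius 85 to 92 mm, cortex 12 to 20 mm below the scalp, 5 mm gap, and three winding layouts. The method is reciprocity with the Sarvas formula for a conducting sphere.

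| Winding assumed | Sham/active, peak | Sham/active, area mean |
|---|---|---|
| One loop, 45 mm | 0.46 to 0.54 | 0.23 to 0.24 |
| Turns at 33 to 60 mm | 0.32 to 0.35 | 0.17 to 0.18 |
| Turns at 25 to 45 mm | 0.32 to 0.35 | 0.19 to 0.20 |

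A second calculation, with gaps of 4 to 12 mm and depths to 25 mm, gave 0.30 to 0.55 at peak and 0.16 to 0.23 on average. Together the ranges are about 0.30 to 0.55 and 0.16 to 0.24.

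By peak field, the table's extremes correspond to 25% × 0.32 = 8% and 25% × 0.54 = 13.5% of maximum output in the active orientation, not to zero. The sham field is also much more confined. The share of modelled cortex above half the active peak rounds to 0.00 under sham, against 0.24 to 0.54 under active.

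**3. What attenuation would do, if there is any**

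Let f be the share of the active effect that the sham delivers. The observed difference is then (1 - f) × the true difference. The article does not give f, so it is varied here. The differences are the ones the article cites to justify its limit, treated for illustration as differences from an inert sham.

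| f | Headache, 28% - 16% = 12 points | Scalp discomfort, 39% - 15% = 24 points |
|---|---|---|
| 0 | 12 | 24 |
| 0.25 | 9 | 18 |
| 0.5 | 6 | 12 |

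The 12-point difference falls to the 10-point limit when 12 × (1 - f) = 10, that is f = 1/6, about 0.17. The field ratios in step 2 are not estimates of f. They are cortical, whereas scalp discomfort arises at the scalp, where no field was computed. No dose-response is given for either.

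**The case against.** A reader might infer that the safety and myelin differences *are* understated. The documents do not support that. It needs a dose-response in which the residual field is active, and none is given. If there is a response threshold above the sham field, nothing is lost.

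The intervention section also says that, at low intensity, only one induced-current direction has lasting effects on excitability, and the active coil is flipped between hemispheres to obtain it. The ratios above compare magnitudes only, so the residual field may be inactive by direction. This stands for the MRI and symptom outcomes as a reason why there may be no loss. It does not settle the matter: no induced-current direction is stated for the sham, and the statement concerns excitability, not adverse reactions.

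Other points for the plan:

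- The wording is partly qualified. Two of the three statements speak of stimulation and not of field, and one has a softening adverb. This is fair, but the blinding section has no such qualifier. The direction may have been meant as away from the brain, but it does not say so.
- Edge-on sham is described as previously used, a trial-quality criterion and effective for blinding naïve participants, with matched sound and timing. That supports its use as a blind. It does not show that it is inert.
- The MRI and symptom contrasts are already called preliminary or exploratory, and adverse events will be tabulated. A confidence interval for one arm is normally a matter for the analysis plan. Its absence is not the fault here. The fault is a safety limit read against a comparator said to deliver nothing.
- The sample size was not set by a power calculation, so no loss of planned power can be claimed.

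**Conclusion.** The point holds as a wrong statement of the comparator's properties, with a conditional consequence. The field direction is reversed as written, which follows from the article's own geometry. The claim that the field is prevented from stimulating or entering the brain is too strong. The modelled residual is about 0.30 to 0.55 of active at peak and 0.16 to 0.24 on average, under a spherical head and assumed head size, cortical depth, gap and winding.

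Whether rTMS-sham differences are attenuated is not shown. With f = 0 there is no loss. With any f above 0, the shift is towards acceptable safety and towards a null on MRI and symptoms. A difference within 10 points, or a null contrast, therefore cannot by itself carry the conclusion. This is a risk to interpretation, not a demonstrated bias, and not a reason to call the sham unusable as a blind.

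**What to change.** 1. In Intervention description {11a}, correct the direction: the sham position puts the field parallel to the scalp.
2. There, in the abstract and in Who will be blinded {17a}, describe the field as reduced and not prevented. Give a modelled residual field for the sham position, with its assumptions.
3. State that each rTMS-sham contrast compares full with reduced field. A difference within 10 points does not alone show acceptable safety, and a null MRI or symptom contrast does not alone show no effect.
4. Base the safety conclusion also on the rTMS arm's absolute adverse-reaction proportion with an exact 95% CI. It will be wide. Trial status reports recruitment closed at 20, so 2:1 allocation gives about 20 × 2/3 ≈ 13 in the rTMS arm. Even zero reactions in 13 leaves an upper limit of 1 - 0.025^(1/13) ≈ 25%.

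The cost is some wording, one field model and one interval. Nothing that participants receive changes. Trial status says that no intervention comparison had been analysed at submission, so on that account the change could be made before results are known. The downside is a slightly less favourable safety conclusion.
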